### **Inclusion Criteria**

- Patients over 18 years with chronic kidney disease (Creatinine Clearance  $\leq$  40 ml / min), and Hb between 11-12 g / dl, serum ferritin <100 mg / dl, or TSAT <20, being treated with a regular (monthly) institution schedule for EPO together with oral iron during the last 6 months before inclusion.

### **Exclusion Criteria**

- Patients with other obvious cause of acute anemia (gastrointestinal bleeding, urological or gynaecological), or other causes of chronic anemia (active malignancy, chronic infections).
- Patients expected to require HD in next 6 months.
- Patients with decompensate heart failure.
- History of allergic reactions to iron preparations and / or anaphylaxis from any cause.
- Patients requiring blood transfusion and blood products for another reason (planned major surgery).
- Pregnant patients.
- Patients with chronic decompensate mental disorders.
- Bedridden patients with dementia syndromes or unable to sign informed consent.
- Patients with a life expectancy of less than a year.

[figure not shown]

[name]; PhD; FASN.  
Professor of Medicine University of Buenos Aires  
Chief of Nephrology.  
Hospital Alemán, [name]  
Buenos Aires (1118)- Argentina  
[contact]  
[contact]  
Mobile [contact]  
E-mail: [contact]

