### *Secondary:*

- To assess the number of hospitalizations pre (six months) and post (six months) intravenous 1g Ferric Carboxymaltose (FERINJECT ®) administration in patients with CKD in pre-dialysis stage.
- To record the need for transfusion pre (six months) and post (six months) intravenous 1g Ferric Carboxymaltose (FERINJECT ®) administration in patients with CKD in pre-dialysis stage.
- To evaluate renal function as measured by Creatinine clearance and proteinuria of 24 hours, pre (six months) and post (six months) intravenous 1g Ferric Carboxymaltose (FERINJECT ®) administration in patients with CKD in pre-dialysis stage.
- To analyze the number of adverse reactions and complications due to intravenous 1g Ferric Carboxymaltose (FERINJECT ®) administration in patients with CKD in pre-dialysis stage.

[figure not shown]

[name]; PhD; FASN.  
Professor of Medicine University of Buenos Aires  
Chief of Nephrology.  
Hospital Alemán, [name]  
Buenos Aires (1118)- Argentina  
[contact]  
[contact]  
Mobile [contact]  
E-mail: [contact]

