## **STATISTICS**

All statistical analyses will be processed through GraphPad Prism version 4.0 (GraphPad Software, Inc. San Diego, CA). Initially, a descriptive statistic of the sociodemographic, clinical and laboratory characteristics will be performed of all the participant patients of the study, directed to describe patient population. Then, calculation of absolute frequencies, proportions, measures of central tendency and dispersion of the involved variables will be performed. When evaluating parameters with a Gaussian distribution, comparisons will be carried out using t-test. For those parameters with a non-Gaussian distribution, comparisons will be performed by non-parametric methods using the Wilcoxon rank sum test. Values will be expressed as mean  $\pm$  SD, and  $p < 0.05$  will be considered significant.

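### The planned-surgery transfusion exclusion has no counterpart before the infusion, so the pre/post comparisons of hospitalizations and transfusions are not like for like

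*Protocol*

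**What the plan says.** Two secondary objectives are before-and-after comparisons in the same patients: "To assess the number of hospitalizations pre (six months) and post (six months) intravenous 1g Ferric Carboxymaltose" and "To record the need for transfusion pre (six months) and post (six months) intravenous 1g Ferric Carboxymaltose". Study Design describes one arm of 30 patients with no control group. The Variables section lists both outcomes as plain numbers of events, with no observation time attached.

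Three Exclusion Criteria look ahead from entry: "Patients requiring blood transfusion and blood products for another reason (planned major surgery"), "Patients expected to require HD in next 6 months" and "Patients with a life expectancy of less than a year". No criterion or counting rule deals with planned surgery, or transfusion for it, in the six months before entry.

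Eligibility requires six prior months of regular EPO with oral iron, so the pre window is always complete. Patient Withdrawal lets the patient or the investigator end participation early, including on account of intercurrent illness that could affect the results.

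The Statistics section says that for Gaussian parameters "comparisons will be carried out using t-test". It assigns the Wilcoxon rank sum test to the others and calls p < 0.05 significant.

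**The concern.** A patient transfused at elective surgery three months before entry is eligible and contributes a pre-period admission and transfusion. A patient with the same operation scheduled three months after entry is barred. Among those enrolled, this kind of event can therefore appear in the pre window but is screened out of the post window wherever it was foreseeable. It bears directly on the two outcomes being compared, and there is no control arm in which the same imbalance would show.

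Unequal observation time adds to this. A patient who leaves at month three brings six months of pre-period events and three months of post-period events to a comparison of raw numbers.

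At stake is a reported fall in hospitalizations or transfusions that comes partly from who was enrolled and how long they were watched.

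**Working it through.** **Plan's own figure.** There is none to reproduce. The sample of 30 is given without an event rate, effect size, SD or power. All rates below are assumptions.

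**Step 1: which exclusions create the imbalance.** Each exclusion removes the whole patient. The question is whether those who remain can still carry the same kind of event in the pre window.
- Planned major surgery with transfusion: yes. No rule prevents or discounts it.
- Dialysis start: no. Everyone enrolled is still pre-dialysis.
- Death or a terminal admission: no. Everyone enrolled is alive.

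Only the first makes the windows unequal. A simple model checks the other two. Let 15% of patients be near dialysis or death, with 0.2 pre-period and 1.0 post-period events each, and let the rest have 0.2 in both windows. Kept in, the post/pre ratio is (0.15 × 1.0 + 0.85 × 0.2) / 0.2 = 0.32 / 0.2 = 1.6. Excluded, it is 0.2 / 0.2 = 1.0. These exclusions remove a natural worsening but do not push post below pre.

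**Step 2: expected size with no drug effect.** Let h be other events per patient per six months, and s the planned-surgery events per patient in a six-month window. Pre mean = h + s, post mean = h, and q = s / (h + s) is the share of pre-period events tied to planned surgery. The post/pre ratio is 1 − q.
- h = 0.2, s = 0.03: 0.20 / 0.23 = 0.87
- h = 0.2, s = 0.05: 0.20 / 0.25 = 0.80
- h = 0.2, s = 0.10: 0.20 / 0.30 = 0.67

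**Step 3: what offsets it.** If other events rise naturally by a fraction g, the ratio becomes (1 − q)(1 + g), which equals 1 when g = q / (1 − q). That is 11% at q = 10%, 25% at q = 20% and 67% at q = 40%. A larger rise reverses the sign: h = 0.2, s = 0.05, g = 0.5 gives 0.30 / 0.25 = 1.20.

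**Step 4: chance of a false favourable result.** Simulation with n = 30, gamma-Poisson counts (shape 1), post rate = pre rate × (1 − q), g = 0 and no drug effect. The table shows the percentage of trials with two-sided p < 0.05 and fewer post events.

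| Pre rate | q | Paired t-test | Rank sum test |
|---|---|---|---|
| 0.6 | 0 | 2.4 | 0.9 |
| 0.6 | 10% | 4.6 | 2.0 |
| 0.6 | 20% | 8.0 | 3.2 |
| 0.6 | 40% | 23 | 13 |
| 1.0 | 0 | 2.5 | 0.4 |
| 1.0 | 10% | 5.3 | 1.2 |
| 1.0 | 20% | 11 | 3.0 |
| 1.0 | 40% | 35 | 15 |

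The t-test figures use 20,000 simulated trials per row and the rank sum figures 6,000. At 0.2 events per six months, the t-test gives about 4% at q = 20% and 9% at q = 40%. The rank sum test treats the two windows as independent samples, which is why it falls below 2.5% at q = 0.

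**Step 5: exposure.** If 10% of patients leave halfway (assumed), post-period observation falls by 0.10 × 0.5 = 5%, and raw post counts fall with it.

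**The case against.** A reader might infer that all three forward-looking exclusions strip events from the post window only, so that both comparisons must favour the drug even when it does nothing. The documents do not support this. The dialysis and life-expectancy exclusions have a match in the pre window, since everyone enrolled is alive and pre-dialysis. If anything, they make the windows more alike.

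The direction is not assured either. Kidney disease may progress over the follow-up. The stable-treatment requirement and the exclusions at entry for bleeding, malignancy, chronic infection and decompensated heart failure may remove patients who had many pre-period events. Step 3 shows that a moderate natural rise cancels or reverses the pull. That argument stands, but opposing biases of unknown size leave a difference that cannot be interpreted; they do not make the comparison sound.

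The magnitude is fairly disputed. The relative reduction equals q by construction, and q = 40% would mean two in five pre-period events were planned major surgery with transfusion, which nothing in the protocol suggests. Sparse counts are not Gaussian, so the plan's own rule leads to the rank sum test, with about half the error rate or less.

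Denominators and early withdrawal are often left to a SAP, which is not shown here. The exposure point is therefore secondary. The eligibility imbalance is fixed in the protocol itself, and correcting it needs the reason for each event to be collected.

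Finally, these are secondary objectives of a small pilot.

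**Conclusion.** The point holds for the planned-surgery exclusion and, as a lesser matter, for unequal observation time. Followed as written, the plan compares two windows that admit different events, and the exclusion on its own lowers post-period counts without any drug effect. The net direction is unknown.

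With 30 patients, no natural rise in events and an assumed 0.6 to 1.0 events per six months, a false favourable result by paired t-test occurs in about 5% of trials at q = 10%, 8 to 11% at q = 20% and 23 to 35% at q = 40%, against a nominal 2.5%. By the rank sum test it is about 1 to 2%, 3% and 13 to 15%. The smaller values of q are the more plausible reading, but the protocol gives no basis for any of them.

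The correction is worth making because it is cheap. The primary ESA objective is not affected.

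**What to change.** Keep the exclusions as they are. Then:

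1. Add a reason-for-event field to the CRF for every hospitalization and transfusion, and complete it for the six months before entry as well.
2. State in the objectives that admissions and transfusions linked to planned major surgery are counted in neither window. Do not also drop events linked to starting dialysis: the pre window has none, so that rule would delete events from the post window only.
3. Express both outcomes as events per patient-month of observation, compare them within patient, and report the difference or ratio with a 95% CI.
4. Label the two comparisons descriptive, and say that without a control group they are not evidence that the drug reduces events.

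The cost is one definition, one CRF field and a few lines of analysis wording. The downside is slightly fewer countable events and possibly a less favourable headline.

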## **STUDY DESIGN**

- Prospective study to 6 months with a single branch of patients who are treated with monthly EPO therapy together with oral iron for at least the last six months before the study and met inclusion criteria.
- From CKD database are randomly selected 30 patients. After signing an informed consent form in duplicate and with witness, duly authorized by the Committee on Education and Research institutions, all patients will receive intravenous 1g Ferric Carboxymaltose (FERINJECT ®) in one dose of 1000 mg on the recommendation of the product.
- On a monthly basis after intravenous 1g Ferric Carboxymaltose (FERINJECT ®) the administration, all patients will be controlled dosage of Hb by HemoCue, in order to dispense the EPO to maintain a baseline Hb level.
- Monthly checks will be carried to register: vital signs and weight control, and record of adverse reactions linked to 1g Ferric Carboxymaltose (FERINJECT ®) administration, registration HemoCue results.
- Before FERINJECT treatment and then every two months, all patients underwent blood control that includes: complete blood count haematimetric indexes, platelet count, serum iron, serum ferritin, TSAT, CRP, urea, creatinine, liver function tests).
- There will be collection of 24-hour urine to measure Creatinine Clearance and proteinuria at baseline and at the end of the study.

[figure not shown]

[name]; PhD; FASN.  
Professor of Medicine University of Buenos Aires  
Chief of Nephrology.  
Hospital Alemán, [name]  
Buenos Aires (1118)- Argentina  
[contact]  
[contact]  
Mobile [contact]  
E-mail: [contact]

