### Visit 2:

- a) Anamnesis and Physical Examination (Vital signs: blood pressure, heart rate, breath rate, etc).
- b) IV Ferinject ® 1000 mg administration.
- c) Evaluation of tolerability and adverse effects.

### Visit 3

- a) Anamnesis and Physical Examination (Vital signs: blood pressure, heart rate, breath rate, etc).
- b) Evaluation of tolerability and adverse effects.
- c) Blood samples for Hb, Htc. RBC, serum ferritin, transferrin saturation, creatinine clearance and proteinuria.

### Visit 4 to 8

- a) Anamnesis and Physical Examination (Vital signs: blood pressure, heart rate, breath rate, etc).
- b) Evaluation of tolerability and adverse effects.
- c) Blood samples for Hb, Htc. RBC, serum ferritin, transferrin saturation, creatinine clearance and proteinuria.
- d) Adjustment of medication according to the Hb and TSAT outcomes.

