### Potential results post FERINJECT ®

### Measure to follow

|                                  |                                  |
|----------------------------------|----------------------------------|
| 1- Hb 12-13 (g/dl) TSAT (%) > 20 | NO Ferinject NO Epo              |
| 2- Hb 12-13 (g/dl) TSAT (%) < 20 | Ferinject 100mg NO Epo           |
| 3- Hb 11-12 (g/dl) TSAT (%) > 20 | NO Ferinject increase Epo 25%    |
| 4- Hb 11-12 (g/dl) TSAT (%) < 20 | Ferinject 200mg NO Epo           |
| 5- Hb 10-11 (g/dl) TSAT (%) > 20 | NO Ferinject increase Epo 25%    |
| 6- Hb 10-11 (g/dl) TSAT (%) < 20 | Ferinject 300mg increase Epo 25% |

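### The dosing table raises EPO 25% for every patient at Hb 11-12 g/dl with TSAT above 20, although the stated goal is to hold baseline Hb, which at entry is 11-12 g/dl

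*Protocol*

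**What the plan says.** **Goal of dosing.** STUDY DESIGN has Hb measured each month after the infusion by HemoCue, "in order to dispense the EPO to maintain a baseline Hb level".

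**Entry state.** The Inclusion Criteria require creatinine clearance of 40 ml/min or less "and Hb between 11-12 g / dl", with low ferritin or TSAT, in patients "being treated with a regular (monthly) institution schedule for EPO" plus oral iron for the previous six months.

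**Dosing rule.** Item d under Visit 4 to 8 is "Adjustment of medication according to the Hb and TSAT outcomes". The table headed Potential results post FERINJECT / Measure to follow comes directly after it. Its six rows are as follows (the percent sign falls outside the quotes of rows 3 and 5).

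- Above the entry band with TSAT above 20, the first row reads "1- Hb 12-13 (g/dl) TSAT (%) > 20 | NO Ferinject NO Epo". Row 2, the same Hb band with TSAT below 20, has the same EPO entry and adds 100 mg of Ferinject.
- Inside the entry band with TSAT above 20, the instruction is "3- Hb 11-12 (g/dl) TSAT (%) > 20 | NO Ferinject increase Epo 25" percent, so a patient whose Hb has not left the entry range gets more EPO.
- One band lower, again with TSAT above 20, the table repeats that action: "5- Hb 10-11 (g/dl) TSAT (%) > 20 | NO Ferinject increase Epo 25" percent. Row 6, the same low band with TSAT below 20, has the same EPO step and adds 300 mg of Ferinject.
- Back inside the entry band, but with TSAT below 20, the EPO entry is a different one: "4- Hb 11-12 (g/dl) TSAT (%) < 20 | Ferinject 200mg NO Epo".

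**Use of the EPO dose.** The primary objective is to find out whether the ESA requirement falls after 1 g of ferric carboxymaltose. STUDY DESIGN describes a single group of 30 patients followed for six months, and METHODS calls the study an open-label pilot.

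**The concern.** An EPO dose measures requirement only if it is titrated to a stated Hb goal. The stated goal is baseline Hb, and patients enter at 11-12 g/dl. A patient who stays at 11.5 with TSAT 25 after the infusion is where the study wants the patient to be, and iron is no longer short. The EPO dose should then be kept or tested downward, but row 3 raises it by 25%, as if Hb had fallen to 10-11.

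There is no control arm. A change in EPO produced by the table therefore cannot be separated from a change produced by the iron. Two staff members could also record different values of the primary outcome for the same patient, depending on whether they follow the goal in STUDY DESIGN or the table, and on how they read *NO Epo*.

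**Working it through.** The plan gives no figure to reproduce. The check sets the table beside the dosing goal.

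**Step 1: what each row does to a current EPO dose D**, under the two possible meanings of *NO Epo*:

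| Row | Hb (g/dl) | TSAT (%) | Ferinject | EPO if *NO Epo* = withheld | EPO if *NO Epo* = no increase |
|---|---|---|---|---|---|
| 1 | 12-13 | >20 | none | 0 | D |
| 2 | 12-13 | <20 | 100 mg | 0 | D |
| 3 | 11-12 | >20 | none | 1.25 D | 1.25 D |
| 4 | 11-12 | <20 | 200 mg | 0 | D |
| 5 | 10-11 | >20 | none | 1.25 D | 1.25 D |
| 6 | 10-11 | <20 | 300 mg | 1.25 D | 1.25 D |

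- Row 3 gives the same result under both readings, and its whole action equals that of row 5.
- Withheld reading: 0 of 6 rows give D, so the table cannot continue a dose.
- No-increase reading: 0 of 6 rows give less than D, so the table cannot lower a dose, in a study that looks for a reduction.

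**Step 2: row 3 against the goal, by the patient's own baseline** (TSAT above 20 throughout; illustrative Hb values within the entry range):

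| Entry Hb | Current Hb | Maintaining baseline implies | Row 3 |
|---|---|---|---|
| 11.5 | 11.5 | keep the dose | +25% |
| 11.1 | 11.9 | keep or lower | +25% |
| 11.9 | 11.1 | an increase is reasonable | +25% |

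The conflict lies in the first two lines: patients at or above their own baseline. The third line is consistent with STUDY DESIGN. The table uses fixed bands and cannot tell the three apart.

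**Step 3: the base for the 25%.** On the withheld reading, take a patient at 12-13 whose EPO is withheld and who then falls to 11-12 with TSAT above 20. Row 3 gives 1.25 x 0 = 0 if the base is the withheld dose, and 1.25 D if it is the last dispensed dose. The protocol text does not say which.

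**Step 4: direction.** Row 3 pushes post-infusion EPO up under either reading. Rows 1, 2 and 4 push it down only if *NO Epo* means withheld. At the same Hb of 11-12, TSAT 19 gives *NO Epo* and TSAT 21 gives +25%. The net effect depends on the meaning of *NO Epo* and on how often patients fall in each row. The document gives neither.

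**The case against.** **Baseline may mean the patient's own value.** If so, raising EPO in someone who has dropped from 11.9 to 11.1 is what STUDY DESIGN asks for. This stands, and it narrows the conflict to patients at or above their own baseline. It does not remove the conflict, because row 3 covers everyone in the band.

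***NO Epo* may be shorthand for no increase.** This also stands as a possibility. A reader might infer that the table has no hold row at all, or that it steers Hb toward about 12 g/dl by stopping EPO above that level and raising it below. Both inferences need the withheld reading. Monthly dosing makes that reading natural, but the text does not define the term. Row 3 does not depend on it.

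**The step could compound.** A reader might take 1.25^5 = 3.05 over Visits 4 to 8 as the size of the inflation. That is a ceiling for a patient who is in row 3 at all five visits, with each increase built on the last. Hb would probably move out of the band as EPO rose. It is not an estimate of bias.

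**TSAT may not be known each month.** STUDY DESIGN schedules TSAT every two months, while Visit 4 to 8 lists it at every visit. If the two-monthly schedule governs, months without TSAT cannot be assigned to row 3 or row 4, and the STUDY DESIGN goal, which permits an unchanged dose, is the usable rule. This limits how often the conflict arises. It does not reconcile the two instructions when TSAT is available.

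**The Hb target may be wider.** The primary objective also mentions keeping Hb in line with international recommendations. That clause may describe only the pre-study period, and it does not make 11-12 a level that calls for an increase. The flow chart is not shown and might hold dosing detail, but it could not make row 3 as written agree with STUDY DESIGN.

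**This is a 30-patient pilot.** That limits what is at stake, but the rule at issue generates the primary outcome.

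**Conclusion.** The point holds on the text with high confidence in this form: row 3 raises EPO by 25% in every patient at Hb 11-12 with TSAT above 20, including those at or above their own baseline, while STUDY DESIGN says EPO is given to hold baseline Hb. It rests on reading the table as the rule applied at Visits 4 to 8, which its position supports, and on no definition of *NO Epo*.

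Six-month EPO still carries some information about requirement, because the table responds to Hb. It is nevertheless partly set by the table and is not the dose that holds baseline Hb. A reader might infer that the plan is biased toward, or against, finding an EPO reduction. The document supports neither: the size and net direction are not determined.

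**What to change.** 1. **Row 3.** Reword to: no Ferinject, maintain the EPO dose; if EPO was withheld at the previous visit, resume at a stated dose (for example the last dispensed dose, or a stated reduction of it); increase by 25% only if Hb is below the patient's baseline by a stated margin, or below 11 g/dl. The resumption dose is essential. Without it, a patient withheld at Hb 12-13 who falls to 11-12 could be maintained on zero EPO, which would favour the study hypothesis.
2. ***NO Epo*.** Define it as withheld that month or as no increase. If it means no increase, add an EPO reduction step at Hb 12-13 (rows 1 and 2).
3. **Base for the 25%.** State the dose from which the increase is calculated.
4. **If a target near Hb 12 is intended,** restate STUDY DESIGN and the primary objective accordingly, and say that the pre/post comparison is not at constant Hb.

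The cost is wording in a few table rows, two definitions and the choice of a margin, with no added visits or tests. The downside is a slower EPO response to Hb drift within 11-12.

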### **Chronogram of visits**

Initial Assessment (visit 1): It will be performed the day the patient enters the study once he/she has read and signed the Informed Consent regarding the participation in the study. In this assessment the following information will be collected:

- a) Demographic and anthropometric data: City and country of residence, age, sex, weight, height, occupation, socioeconomic strata.
- b) Medical History: Diagnosis associated.
- c) Physical Examination (Vital signs: blood pressure, heart rate, breath rate, etc).
- d) Blood samples for Hb, Hct. RBC, serum ferritin, transferrin saturation, creatinine clearance, and proteinuria.

[figure not shown]

[name]; PhD; FASN.  
 Professor of Medicine University of Buenos Aires  
 Chief of Nephrology.  
 Hospital Alemán, [name]  
 Buenos Aires (1118)- Argentina  
 [contact]  
 [contact]  
 Mobile [contact]  
 E-mail: [contact]

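### The renal objective compares six months before with six months after infusion, but the protocol describes no renal value from before study entry, so CKD progression cannot be separated from treatment

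*Protocol*

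**What the plan says.** The relevant secondary objective (Protocol, Objective, Secondary) is "To evaluate renal function as measured by Creatinine clearance and proteinuria of 24 hours, pre (six months) and post (six months") the 1 g infusion.

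The data available for it are set out in three places:

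- **Study Design:** "There will be collection of 24-hour urine to measure Creatinine Clearance and proteinuria at baseline and at the end of the study". The same section adds a laboratory panel that includes serum creatinine: "Before FERINJECT treatment and then every two months, all patients underwent blood control".
- **Chronogram of visits, visit 1 (day of study entry):** "Blood samples for Hb, Hct. RBC, serum ferritin, transferrin saturation, creatinine clearance, and proteinuria". The infusion follows at visit 2.
- **Chronogram of visits, visit 3 and visits 4 to 8:** "Blood samples for Hb, Htc. RBC, serum ferritin, transferrin saturation, creatinine clearance and proteinuria".

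The design is a "Prospective study to 6 months with a single branch of patients", 30 in number and open label. Entry requires creatinine clearance of 40 ml/min or less. The Statistics section says "When evaluating parameters with a Gaussian distribution, comparisons will be carried out using t-test", with a Wilcoxon rank sum test for other parameters and significance at p < 0.05. Data Collect Methodology describes direct evaluation of patients and does not mention retrieving earlier renal results.

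**The concern.** Hospitalizations and transfusions can be counted in a six-month window on either side of the infusion. Renal function in advanced CKD is different, because it can drift without any new treatment. A single level before infusion does not show what the level would have been six months later without the drug; the earlier rate of change is needed for that. If the plan is followed as described, the test answers whether clearance changed over six months, not whether the infusion altered its course. A fall could be progression alone. A stable value could be a benefit offset by progression. An analysis plan cannot repair this later if the earlier values were never gathered.

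**Working it through.** **1. Renal values by time**

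| Period | Described in the protocol |
|---|---|
| Six months before entry | none |
| Visit 1, before infusion | clearance, proteinuria |
| Visits 3 to 8 | clearance, proteinuria (Chronogram) |
| Every two months after infusion | serum creatinine (Study Design) |
| End of study | 24-hour clearance, proteinuria (Study Design) |

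A post-infusion slope can be computed. A pre-infusion slope cannot.

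**2. What the contrast estimates**

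Let D be the six-month natural change and δ the drug effect. The expected value of end minus baseline is D + δ. One arm gives one equation in two unknowns. If a value six months before infusion is added and the decline is linear, the pre-period change estimates D, the post-period change estimates D + δ, and their difference estimates δ.

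**3. How large the confounding could be**

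The protocol has no power calculation, SD or rate of decline to reproduce. Assumptions, none from the documents: decline d of 1, 2 or 3 ml/min over six months (2, 4 or 6 per year); SD of the within-patient change s of 3, 5 or 8 ml/min; two-sided paired t-test. From the documents: n = 30, alpha 0.05.

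SE = s/√30, which is 0.55, 0.91 and 1.46 ml/min. The test statistic has noncentrality d/SE on 29 df. The chance of p < 0.05 when δ = 0 is:

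| Decline over 6 months | s = 3 | s = 5 | s = 8 |
|---|---|---|---|
| 1 ml/min | 42% | 19% | 10% |
| 2 ml/min | 94% | 56% | 26% |
| 3 ml/min | 100% | 89% | 51% |

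At s = 5, an observed mean fall exactly equal to the decline gives:

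- 1/0.913: t = 1.10, p about 0.28
- 2/0.913: t = 2.19, p about 0.04
- 3/0.913: t = 3.29, p about 0.003

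The low end is therefore not significant in a typical trial, though the error rate still exceeds 5%.

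**4. The contrast of changes**

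With one value at each of three times and independent error variance v, the post change has variance 2v. Post change minus pre change has weights 1, −2, 1 and variance 6v. The SE rises by √3, at s = 5 from 0.91 to 1.58 ml/min. In simulation under linear decline (20,000 runs per scenario) the false-positive rate was 4.8% to 5.3% in all nine scenarios.

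**5. Effect of selecting on clearance**

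That simulation ignores the entry limit of 40 ml/min. If the baseline is also the qualifying value, its error enters the contrast with weight −2. For normal data the resulting bias is

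2 (v/σ) φ(z)/Φ(z), with z = (40 − m)/σ,

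where m is the mean clearance of candidates before selection and σ the SD of measured clearance. Take v = 25/2 = 12.5 (s = 5) and a true SD of 15, so σ = √(225 + 12.5) = 15.41:

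- m = 30: z = 0.649, φ/Φ = 0.436, bias = 2 × 12.5/15.41 × 0.436 = 0.71 ml/min
- m = 45: z = −0.324, φ/Φ = 1.015, bias = 1.65 ml/min

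Both are toward apparent benefit, at 0.4 to 1.0 of the 1.58 SE. A narrower population (true SD 10, σ = 10.61, m = 45, φ/Φ = 1.120) gives 2.64 ml/min. Half of each bias also enters end minus baseline, partly offsetting a real decline; the table in step 3 leaves this out.

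**The case against.** A reader might infer that renal function is measured only at baseline and at the end. The documents do not support that: the Chronogram lists clearance and proteinuria at visits 3 to 8, and Study Design has creatinine every two months. These values improve the post-infusion estimate but supply no pre-infusion course.

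A reader might also infer that the plan would attribute a decline to Ferinject. It does not say so. The objective is only to evaluate, it is secondary, and the study is a pilot. This limits how firmly the consequence can be put, but a p-value threshold is still applied to a change that mixes two causes.

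It is fair to say that the absence of earlier values cannot be fully verified. The same pre/post wording covers hospitalizations and transfusions, which must be collected retrospectively. Patients come from a CKD database, and the data form and flow chart are not visible. The text as it stands describes no retrieval of renal results.

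The size rests on assumed figures. Patients expected to need haemodialysis within six months are excluded, which removes the fastest progressors. The plan does not say that its t-test is paired, and the rank sum test it names is for independent samples and would be less sensitive to a small drift. All of this stands, so the percentages are illustrative.

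The strongest objection is to the remedy: comparing changes around a baseline that also decided eligibility builds in regression to the mean. That stands too, and the fix has to guard against it.

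**Conclusion.** The point holds in a limited form. The stated six-month comparison cannot be made from the renal data that the protocol describes, and a change from baseline in one arm cannot be separated from progression in either direction. The illustrated false-positive rate of about 10% to 100% assumes a decline of 1 to 3 ml/min over six months, an SD of change of 3 to 8 ml/min, a paired test and no selection effect. It shows that the problem may be material, not that a false renal finding is certain. Separately, Study Design and the Chronogram disagree on how often clearance and proteinuria are measured. For a secondary objective in a pilot this should be corrected, but it does not affect the primary aim.

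**What to change.** 1. **Collect pre-infusion values.** Extract from the CKD database the serum creatinine values from the six months before infusion, with clearance and proteinuria where available. Compare each patient's post-infusion slope with the pre-infusion slope, using the same creatinine-based measure in both periods. Use all available values, or a baseline separate from the one that qualified the patient at 40 ml/min or less, to limit regression to the mean.
2. **Otherwise describe only.** Where pre-period values are missing, report change from baseline without a significance claim and state that it includes natural progression.
3. **Reconcile the schedule.** Study Design gives 24-hour urine at two times, while the Chronogram lists clearance and proteinuria at visits 1 and 3 to 8 under blood samples and names no renal test at visit 9. State which measurement is made, by which method and when.

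The cost is a short chart extraction per patient and a few sentences in the objective, schedule and statistics sections. The statistical price is precision: the SE rises by about √3 with one value per time point, so a modest effect may stay undetected. Some patients will lack earlier values, and a serum-based measure may have to stand in for the 24-hour measure named in the objective.
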